### Visits and follow-ups

All participants will be followed up for a period of 12 months after treatment initiation (Figure 1).

**Figure 1 fig1:**
[figure not shown]
Study protocol timeline. QD, quit day.

After the baseline visit, two visits (visit 1 at day 7 and visit 2 at the end of treatment, day 25) and three follow-ups (visit 3 at 3 months, visit 4 at 6 months, and visit 5 at 12 months) will be conducted (see Table 1). Visits 1, 2, and 3 will be conducted face-to-face. The last two visits (visits 4 and 5) will be conducted via telephone.

**Table 1 tab1:** Protocol timeline procedure of visits and follow-up for patients enrolled in the CITOSP trial.

Procedure	Visit 0	QD*	Visit 1	Visit 2^§^	Visit 3	Visit 4	Visit 5
Informed consent	√						
Inclusion/exclusion criteria	√						
Demographic characteristics	√						
Clinical history	√						
Smoking history and status	√						
Cytisine treatment		√	√	√			
Adverse events			√	√	√	√	√
Adverse drug reactions			√	√	√	√	√
Self-reported abstinence (PPA)			√	√	√	√	√
Biochemically verified abstinence (exhaled CO)			√	√^#^	√^#^		

QD, quit day.

PPA, point prevalence abstinence.

CO, carbon monoxide.

^#^Only if the visit is in person.

*First day of treatment. ^§^Stop treatment.

Each control visit resulted in the collection of the following records:

Visit 0 (baseline visit): informed consent dated and signed, participant identification code, and socio-demographic characteristics of the participant (age, sex, education, and occupation). Smoking history: age at which cigarettes were first smoked and efforts to quit smoking (number of times, date of last attempt, and use of some drugs to quit smoking). Smoking Status: average amount of cigarettes smoked in the last month, average cigarettes for the year, the score obtained in the FTND test, and use of other forms of nicotine delivery (for example, e-cigarettes). Clinical history: pathologies and ongoing pharmacological treatments. Integrated therapeutic: This statement outlines the non-pharmacological approaches used in the study to help patients, including counseling, cognitive-behavioral education, lifestyle changes, and the possible use of smoking cessation tools.

QD (first day of abstinence): start of integrated therapeutic plan with CYT.

Visit 1 (7^th^ from QD): continuation of the integrated therapeutic plan with CYT, evaluation of AEs, evaluation of ADRs, evaluation of PPA, number of cigarettes smoked (in case of quit failure), and exhaled CO.

Visit 2 (25^th^ day from QD): end of treatment with CYT, evaluation of AEs, evaluation of ADRs, evaluation of PPA, and exhaled CO.

Visit 3 (first follow-up, 3 months from QD): evaluation of AEs, evaluation of ADRs, evaluation of PPA, number of cigarettes smoked (in the case of failure to quit), and exhaled CO.

Visit 4 (second follow-up, 6 months from QD): evaluation of AEs, evaluation of ADRs, evaluation of PPA, and number of cigarettes smoked (in the case of failure to quit).

Visit 5 (third follow-up, 12 months from QD): evaluation of AEs, evaluation of ADRs, evaluation of PPA, and number of cigarettes smoked (in the case of failure to quit).

### Cytisine dosing schedule

The West dosing schedule consisted of six 1.5 mg capsules per day (one capsule every 2 h) for 3 days (days 1 to 3), five capsules per day for 9 days (days 4 to 12), four capsules per day for 4 days (days 13 to 16), three capsules per day for 4 days (days 17 to 20), and two capsules per day for the final 5 days (days 21 to 25) (see Table 2). The target quit date was scheduled for the first day of treatment (day 1) (7).

**Table 2 tab2:** West dosing schedule (7).

Day of treatment	N° of capsules/die	Frequency of administration
Days 1–3	6	1 capsule every 2 h
Days 4–12	5	1 capsule every 2.5 h
Days 13–16	4	1 capsule every 3 h
Days 17–20	3	1 capsule every 4 h
Days 21–25	2	1 capsule every 6 h

In the case of patients with stage IV or V chronic kidney failure, the CYT dosing schedule consisted of three 1.5-mg capsules per day for 12 days (days 1 to 12), two capsules per day for 8 days (days 13 to 20), and finally one capsule per day for the last 5 days (days 21 to 25) (see Table 3).

**Table 3 tab3:** Cytisine dosing schedule adapted to patients in stage IV or V chronic kidney failure.

Day of treatment	N° of capsules/die	Frequency of administration
Days 1–12	3	1 capsule every 4 h
Days 13–20	2	1 capsule every 6 h
Days 21–25	1	1 capsule every 12 h

Concomitant medication use during CYT treatment will be allowed, evaluated, and documented at each visit, and any possible interactions with CYT will be verified.

### Carbon monoxide measurement

The exhaled CO concentration will be measured using the piCOTM Smokerlyzer® (Bedfont Instruments; Kent, United Kingdom), a non-invasive method for assessing the smoker status. It has been reported that the concentration of CO is closely related to the concentration of carboxyhemoglobin in smokers’ and non-smokers’ blood. The piCOTM Smokerlyzer® measures CO levels in the air in parts per million (ppm) based on the conversion of CO to carbon dioxide (CO_2_) on a catalytically active electrode (33).

Scores from 0 ppm to 6 ppm confirm that patients have not smoked cigarettes in previous days before the visit, scores 7 ppm and 8 ppm indicate that patients are light smokers; scores greater or equal to 9 ppm confirm that patients are heavy smokers.

### Sample size and statistical analysis

Assuming an overall incidence of all AEs and ADRs equal to 20% as reported by Hajek et al. (28), 264 subjects will be needed to produce a bilateral confidence interval of 95% with an amplitude of 10%. This number will be increased to 300 subjects to compensate for a potential loss of 14% of subjects during the 12-month follow-up. To recruit 300 subjects, it will take 36 months. The total duration of the study will be 4 years.

All variables recorded in the study will be presented using the plus descriptive statistic appropriate to their nature. Continuous variables will be presented with mean and standard deviation with median and interquartile distance based on their distribution; ordinal and categorical variables will be presented with frequency and percentage.

To assess the safety of treatment with CYT, the incidence of AEs and ADRs will be evaluated, with respective 95% confidence intervals (CIs) up to the end of treatment (day 25) and up to 12 months from the start of the treatment (quit day). The percentage of subjects will be calculated to assess the compliance of patients with CYT treatment who respected their dosage schedule with the respective 95% CI.

To evaluate the efficacy of CYT treatment, the percentage of subjects who reported abstinence in the previous 7 days and 15 days (7-day PPA and 15-day PPA) before each study timepoint will be calculated. For in-person visits and follow-ups, the PPA will be biochemically verified through exhaled CO measurement.

The efficacy will also be studied at a multivariate level to assess whether the positive/negative outcome of the treatment is associated with certain demographic and/or clinical factors. For this type of analysis, they will construct logistic regression models by setting the (yes/no) relapse evaluated as dependent variables according to the reported and objective efficacy criteria at the end of treatment (25^th^ day from the start of treatment) and 12 months from the start of treatment. The independent variables will be chosen based on the assumptions of experimenters on possible predictors of efficacy, including the result of the FTND, the ward, the primary cause of admission, sex, age, education, occupation, age in which the person started smoking, and number of previous smoking cessation attempts.

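### The 300 subjects allow for a 12% loss of those enrolled, not the stated 14%; the effect on the 12-month precision is minor

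*Protocol article*

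**What the plan says.** All the figures stand in the Protocol article under Sample size and statistical analysis.

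- Incidence: "Assuming an overall incidence of all AEs and ADRs equal to 20" per cent.
- Precision: "264 subjects will be needed to produce a bilateral confidence interval of 95% with an amplitude of 10" per cent. Amplitude is read here as the full width of the interval, and the working shows that this reading reproduces 264. The type of interval is not named.
- Allowance for loss: "This number will be increased to 300 subjects to compensate for a potential loss of 14% of subjects during the 12-month follow-up".
- Use: the incidence of adverse events and adverse drug reactions is to be reported with 95% confidence intervals "up to the end of treatment (day 25) and up to 12 months from the start of the treatment (quit day"). Safety is the primary objective.

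**The concern.** The text states the purpose of raising 264 to 300, so the step can be checked: after the stated loss, at least 264 subjects should remain. Patients lost to follow-up are lost from the enrolled cohort, so the natural base for a 14% loss is 300. On that base the remainder falls below the number that the plan itself calls necessary.

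What is at stake is the consistency of the sample-size justification for the primary objective. When the achieved precision is reported, it will be compared with this paragraph, and the loss rate that the paragraph claims to absorb is larger than the one it does absorb.

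**Working it through.** **Inputs, all from Sample size and statistical analysis:** incidence p = 0.20; two-sided 95% interval; full width 0.10; required n = 264; enrolled N = 300; loss d = 0.14 over 12 months.

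**Step 1: reproduce 264.** The smallest n with interval width at or below 0.10 at p = 0.20 depends on the interval.

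| Interval | Smallest n | Width at 258 | Width at 264 |
|---|---|---|---|
| Exact (Clopper-Pearson) | 264 | 10.11% | 9.99% |
| Wilson, continuity-corrected | 264 | 10.11% | 9.99% |
| Wald, continuity-corrected | 266 | 10.15% | 10.03% |
| Agresti-Coull | 247 | 9.77% | 9.66% |
| Wald | 246 | 9.76% | 9.65% |
| Wilson | 245 | 9.73% | 9.62% |

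The Wald figure, for example, is 1.96² × 0.20 × 0.80 / 0.05² = 245.9, so 246. The exact width uses the beta quantiles with x = 0.20n events: upper limit Beta(0.975; x + 1, n − x) minus lower limit Beta(0.025; x, n − x + 1). It is 10.01% at n = 263 and 9.99% at n = 264. The stated 264 is therefore reproduced by the exact interval, and also by the continuity-corrected Wilson interval.

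**Step 2: apply the stated loss to the stated enrolment.** N × (1 − d) = 300 × 0.86 = 258. Shortfall: 264 − 258 = 6.

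**Step 3: enrolment needed for the stated loss.** 264 / (1 − 0.14) = 264 / 0.86 = 306.98, so 307, which is 7 more than 300.

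**Step 4: loss that 300 does absorb.** 1 − 264 / 300 = 36 / 300 = 0.12. Check: 300 × 0.88 = 264.

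**Step 5: where 14% may come from.** The increase is 36 subjects. As a share of 264 this is 36 / 264 = 13.6%, which rounds to 14%. As a share of the 300 enrolled it is 12%. Multiplying gives 264 × 1.14 = 300.96, which is close to 300 but would round to 301.

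**Step 6: effect on precision.** With the exact interval the width goes from 9.99% at 264 to 10.11% at 258, a difference of 0.12 percentage points.

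**The case against.** A reader might infer that the precision target fails, or that the stated sample size, loss and precision cannot all be true. The document does not support either. The width is given to the whole per cent, and 10.11% still rounds to 10%. The threshold is also finer than whole patients allow: 20% of 264 is 52.8 people, and 53 events in 264 already give an exact width of 10.007%, while 50 events in 258 give 9.999%. A change of one or two events matters as much as the 6 subjects.

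The interval is not named either. With a Wald, Wilson or Agresti-Coull interval, 258 subjects give 9.73% to 9.77% and meet the target. That the exact method was used is a plausible inference from the match to 264, not a stated fact. Leaving the method unnamed is not a fault here, because that choice may sit in an analysis plan or full protocol that is not shown.

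A reader might also carry the shortfall over to the day-25 incidence. The 14% is a loss over 12 months, and no loss by day 25 is stated. If it is 12% or less, at least 264 remain. Even at 12 months, a patient lost late will have contributed adverse-event data at earlier visits, and the document does not say that such patients leave the denominator.

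Finally, a reader might take it as established that 264 was multiplied by 1.14. A round target of 300, with the increase of 36 described as 14% of 264, fits equally well.

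All of this limits the consequence. It does not rescue the sentence: on the ordinary reading of a loss among enrolled subjects, 300 does not compensate for 14%. Under any interval, 258 is below the number that the plan says it needs.

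**Conclusion.** The allowance for loss is misstated. At a 14% loss of those enrolled, 300 subjects leave 258, which is 6 below 264. The 300 covers 12%, and 14% would need 307. The most likely explanation is that the percentage was expressed relative to 264 instead of relative to enrolment.

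The effect is minor: about 10.1 points of width instead of 10.0 for the 12-month incidence. This rests on three assumptions: the true incidence is 20%, the interval is the exact one, and patients lost by 12 months are dropped from the denominator. No shortfall is shown at day 25. The study is single-arm and its sample size is set by the width of an interval, so no power claim is affected.

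**What to change.** Keep 300 and replace the sentence on loss with wording such as: *300 subjects allow for a loss of 12% of those enrolled; if 14% are lost by 12 months, 258 remain and the 95% CI width at 20% incidence is about 10.1% (exact method).* If the sponsor's calculation used a different interval, the width quoted should be the one for that interval.

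The cost is one sentence. No extra patients are needed, and the design and analysis do not change. Enrolling 307 would also make the text correct, but a gain of about 0.1 percentage points in width does not call for it.

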### Clinical endpoints

The primary endpoint of the study is to assess the safety of CYT adverse events (AEs) or adverse drug reactions (ADRs) reported by participants, which will be collected.

AEs are defined by the Italian Legislative Decree 211/2003 as “any harmful clinical event that occurs in a patient or in a person involved in a clinical trial that has been given a medicinal/device product and does not necessarily have a causal relationship with this treatment.” Indeed, ADRs are defined as follows: “all untoward and unintended responses to an investigational medicinal product related to any dose administered.” The definition also covers “medication errors and uses outside what is foreseen in the protocol, including misuse and abuse of the product” (Directive 2001/83/EC, Ministerial Decree 30 April 2015-GU No. 143).

For the European Regulation (Directive 2001/83/EC), serious adverse events (SAEs) or serious adverse reactions (SARs) are defined as “any unwanted medical event or device failure that results in the following outcomes: is fatal (causes death), is life-threatening (an event in which the patient was at risk of death at the time of the event), requests hospitalization or extension of hospitalization in progress, determines persistent or significant degree disability or incapacity, corresponds to a congenital anomaly/birth defect, is medically significant, or requires intervention to prevent one of the other outcomes listed above.”

If an AE occurs, the physician, supported by the clinical monitor (CM), will evaluate the event/treatment correlation to determine if an AE could be an ADR. At each visit or follow-up, AEs and ADRs reported by participants will be recorded by the CM in the CRF. In case of an ADR, the physician or the CM will fill out the online reporting form on the AIFA website (https://servizionline.aifa.gov.it/schedasegnalazioni/#/). The textual descriptions will be summarized in the report forms and will be coded according to standard terms in the Medical Dictionary for Regulatory Activities (MedDRA).

The secondary endpoints of the study are to assess the efficacy and compliance of CYT treatment. Self-reported 7-day and 15-day point prevalence abstinence (PPA) will be assessed at each study timepoint. A relapse will occur when patients smoke 7 or more cigarettes for 7 consecutive days or 2 consecutive weeks.

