Biochemically verified abstinence will be evaluated using exhaled carbon monoxide (CO) measurement during in-person visits. A relapse is considered when CO value ≥9 ppm (non-smoker value <4.5 ppm) (30, 31).

To assess CYT treatment compliance, patients will be provided a study diary in which capsule intake or self-reported treatment adherence can be reported.

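### The day-25 objective relapse outcome appears to rest on exhaled CO alone, so a reported relapse with CO below 9 ppm would be coded as not relapsed; CO is also said to verify a 15-day window it cannot cover

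*Protocol article*

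**What the plan says.** Clinical endpoints gives two relapse criteria, one after the other. The first rests on self-report: "A relapse will occur when patients smoke 7 or more cigarettes for 7 consecutive days or 2 consecutive weeks". The second rests on exhaled CO: "A relapse is considered when CO value ≥9 ppm (non-smoker value <4.5 ppm". Nothing joins them, and no rule covers a patient who meets one and not the other.

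Sample size and statistical analysis uses both. Relapse (yes/no) is the outcome of logistic regression models, "evaluated as dependent variables according to the reported and objective efficacy criteria at the end of treatment" and again at 12 months. Listed predictors include the FTND score, ward, cause of admission, sex and age.

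The same section defines the efficacy percentages separately, as "the percentage of subjects who reported abstinence in the previous 7 days and 15 days (7-day PPA and 15-day PPA" before each timepoint. It then adds: "For in-person visits and follow-ups, the PPA will be biochemically verified through exhaled CO measurement". The two windows are not distinguished.

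Carbon monoxide measurement interprets the readings: "Scores from 0 ppm to 6 ppm confirm that patients have not smoked cigarettes in previous days before the visit", and "scores 7 ppm and 8 ppm indicate that patients are light smokers". Readings of 9 ppm or more denote heavy smokers.

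**The concern.** There are two linked problems.

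- **Relapse model.** If the objective outcome is CO alone, a patient's own report of relapse is set aside whenever the reading is below 9 ppm. The missed relapses would not be a random subset. They would be mostly lighter smokers and those who had not smoked for some hours before the visit. The model's purpose is to find predictors of outcome, and some candidates, the FTND score above all, are plausibly related to how heavily a patient smokes. An outcome that detects heavier smokers preferentially can create or inflate such associations.
- **Verified abstinence.** Saying that CO verifies 15-day abstinence claims more than the protocol's own account of the test, which speaks only of the preceding days. A reader of the results would take the 15-day figure to be biochemically confirmed over its whole window.

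**Working it through.** The plan gives no computed figure on this point. The sample size of 264 rests on adverse-event incidence and is not touched.

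**1. What the objective criterion is.** Table 1 lists two abstinence procedures, self-report and exhaled CO. CO is therefore the only objective one.

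**2. Coding at day 25 if the criteria are separate outcomes.**

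| Reported relapse rule | CO | Reported model | Objective model (CO alone) | Reported OR CO-positive |
|---|---|---|---|---|
| met | 9 ppm or more | relapse | relapse | relapse |
| met | below 9 ppm | relapse | **not relapsed** | relapse |
| not met | 9 ppm or more | not relapsed | relapse | relapse |
| not met | below 9 ppm | not relapsed | not relapsed | not relapsed |

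The problem lies in the second row only.

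**3. Whether the second row can occur.** The protocol's own CO statements, side by side:

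| Reading | Clinical endpoints | Carbon monoxide measurement |
|---|---|---|
| below 4.5 ppm | non-smoker value | no recent smoking |
| 4.5 to 6 ppm | neither non-smoker nor relapse | no recent smoking |
| 7 to 8 ppm | neither non-smoker nor relapse | light smoker |
| 9 ppm or more | relapse | heavy smoker |

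A patient at 7 to 8 ppm is a smoker in one section and not relapsed by CO in the other. This needs no outside figure. The article does not tie the light-smoker band to a cigarette count, so overlap with the reported relapse rule is possible rather than stated.

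**4. Effect on a predictor.** Let R(f) be the true relapse probability at FTND score f, and S(f) the probability that a relapsed patient reads 9 ppm or more. Ignoring false positives,

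P(objective relapse | f) = R(f) × S(f).

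The risk ratio between scores f1 and f0 is then

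[R(f1)/R(f0)] × [S(f1)/S(f0)].

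If S rises with f, the ratio is inflated by S(f1)/S(f0), and it exceeds 1 even when R is flat. That S rises with FTND is an assumption: more dependent patients who relapse smoke more. The documents give nothing from which to estimate S.

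**5. How far back a reading reaches.** The documents give neither a CO half-life nor a starting level. Assumptions: first-order decline, half-life h of 2 to 8 h, starting level C0 of 15 to 60 ppm. Time to fall to cut-off c is t = h × log2(C0/c).

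| Cut-off c | Shortest (h = 2, C0 = 15) | Longest (h = 8, C0 = 60) | Longest as share of 168 h (7 days) | Longest as share of 360 h (15 days) |
|---|---|---|---|---|
| 9 ppm | 2 × log2(15/9) = 1.5 h | 8 × log2(60/9) = 21.9 h | 13.0% | 6.1% |
| 6 ppm | 2 × log2(15/6) = 2.6 h | 8 × log2(60/6) = 26.6 h | 15.8% | 7.4% |
| 4.5 ppm | 2 × log2(15/4.5) = 3.5 h | 8 × log2(60/4.5) = 29.9 h | 17.8% | 8.3% |

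In reverse, the half-life needed to read 9 ppm a full window after the last cigarette is window / log2(C0/9):

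- 7 days: 168 / log2(20/9) = 145.8 h from 20 ppm; 168 / log2(60/9) = 61.4 h from 60 ppm.
- 15 days: 360 / log2(20/9) = 312.5 h; 360 / log2(60/9) = 131.5 h.

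These lie far outside the assumed 2 to 8 h, so the conclusion does not depend on the exact values.

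**The case against.** - **Separate use of the criteria is not stated.** This stands as a limit. The analysis section does not say that CO alone defines an outcome. The plural wording for models and dependent variables favours two outcomes, but a combined criterion is not excluded. The treatment of discordant cases may also be in the full protocol. Even so, the article does fix a CO relapse rule with no link to self-report and names an objective criterion for the model, so the likelier reading follows from what is written.
- **Relapse is not the same as any smoking.** A reader might infer that anyone who smoked within the window and reads low is wrongly coded. The documents do not support that. The reported rule requires sustained smoking, so a patient who admits a cigarette two days earlier has failed 7-day PPA but has not relapsed on the reported criterion either. Only patients who meet the reported relapse rule and read below 9 ppm are affected.
- **The PPA percentages are sound against admitted smoking.** A reader might infer that the efficacy percentages are overstated. They start from reported abstinence, so an admitted smoker never enters the numerator and CO can only remove claimed abstainers. The regression looks for predictors and estimates no abstinence rate. Smoking that is neither admitted nor detected stays hidden under any rule that uses these data.
- **The half-life is not in the documents.** Correct, and it is labelled as an assumption. The 7 to 8 ppm discrepancy and the gap between the preceding days and 15 days stand without it.
- **Efficacy is secondary.** True; the primary objective is safety. This limits the weight of the point.

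**Conclusion.** The point holds in a limited form. On the likelier reading of the analysis section, the day-25 objective model codes a patient as not relapsed when the patient reports relapse but reads below 9 ppm, including readings the protocol itself calls light smoking. This under-counts relapse in that outcome and can distort predictor associations, upward for FTND if detection rises with dependence. The number of patients affected cannot be derived from the documents.

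The claim that CO verifies 15-day abstinence is not supported by the protocol's own description. Under the assumed half-life and starting levels, a reading covers roughly the last day (1.5 to 29.9 h over the three cut-offs). CO can contradict a claim of abstinence, but it cannot confirm 7 days, still less 15.

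The PPA percentages, the safety analysis and the sample size are not affected. The relapse coding is limited here to day 25: the 12-month visit is by telephone, with no CO reading, which is a separate matter.

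**What to change.** In Clinical endpoints and in Sample size and statistical analysis:

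1. Code the day-25 objective (verified) relapse as present if the reported relapse rule is met **or** CO is at or above one chosen cut-off, so that reported relapse overrides a low reading.
2. Define verified PPA as reported abstinence in the window **and** CO below that same cut-off.
3. State that CO corroborates recent abstinence only, and label 15-day PPA as self-reported.
4. Reconcile the CO bands between Clinical endpoints and Carbon monoxide measurement (4.5, 6, 7 to 8 and 9 ppm), and bring the statement about the preceding days into line with point 3.

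The cost is wording only: no new data, visits or patients. The OR rule keeps relapse as the modelled outcome and does not replace it with strict abstinence. The downside is that the verified relapse rate will be somewhat higher than by CO alone.

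### CO verification of abstinence depends on contact mode at day 25 and month 3 and is absent at 6 and 12 months, and the analysis section does not keep reported and verified abstinence apart

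*Protocol article*

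**What the plan says.** **Outcomes (Protocol article, Clinical endpoints).** Two measures are described in turn. First: "Self-reported 7-day and 15-day point prevalence abstinence (PPA) will be assessed at each study timepoint". Then: "Biochemically verified abstinence will be evaluated using exhaled carbon monoxide (CO) measurement during in-person visits". The rule attached to CO is "A relapse is considered when CO value ≥9 ppm (non-smoker value <4.5 ppm").

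**Contact mode (Visits and follow-ups).** The text says "Visits 1, 2, and 3 will be conducted face-to-face" and "The last two visits (visits 4 and 5) will be conducted via telephone". Table 1 has one row for self-reported abstinence, ticked at visits 1 to 5, and another for biochemically verified abstinence, ticked at visits 1 to 3. In that second row the ticks at visits 2 and 3, but not at visit 1, carry the footnote "Only if the visit is in person".

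**Analysis (Sample size and statistical analysis).** The efficacy result is "the percentage of subjects who reported abstinence in the previous 7 days and 15 days (7-day PPA and 15-day PPA) before each study timepoint". The next sentence is "For in-person visits and follow-ups, the PPA will be biochemically verified through exhaled CO measurement". Logistic models then take relapse (yes/no) as the dependent variable, judged by both a reported and an objective criterion, at day 25 and at 12 months.

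**The concern.** The footnote has no function unless remote contact is foreseen at day 25 and month 3, so it conflicts with the statement that those visits are face-to-face.

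The analysis section attaches verification to the PPA itself, not to a second outcome. Take two participants at month 3 who both smoke and both claim seven days of abstinence. One attends, has a CO of 9 ppm or more and is a relapse. The other is telephoned, has no CO reading, and nothing in the text stops the claim counting as abstinence. The percentage then reflects how people were contacted as well as whether they smoked.

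The study has one arm, so no between-group contrast can cancel such an error. The abstinence percentages are themselves the efficacy result.

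The 12-month model has a further problem. CO is the only objective measure described, and none is taken at 12 months.

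**Working it through.** **Step 1. Availability of CO by visit**

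| Visit | Contact mode in the text | CO in Table 1 | What verification can do |
|---|---|---|---|
| 1 (day 7) | face-to-face | yes | overturn a claim |
| 2 (day 25) | face-to-face | only if in person | overturn a claim only if the participant attends |
| 3 (month 3) | face-to-face | only if in person | as visit 2 |
| 4 (month 6) | telephone | none | nothing |
| 5 (month 12) | telephone | none | nothing |

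Columns 2 and 3 disagree at visits 2 and 3. The objective criterion modelled at month 12 has no measurement behind it.

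**Step 2. The CO cut-off.** Clinical endpoints gives relapse at 9 ppm or more and a non-smoker value below 4.5 ppm. Carbon monoxide measurement treats 0 to 6 ppm as not having smoked, 7 and 8 ppm as light smoking, and 9 ppm or more as heavy smoking. A reading of 7 or 8 ppm is therefore smoking under one section and not a relapse under the other. A reading of 5 or 6 ppm is non-smoking under one section and above the non-smoker value of the other. Verified abstinence is not fixed until these agree.

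**Step 3. Size if the two measures are pooled.** The documents give no abstinence rate, misreporting rate or remote-contact rate, so all three inputs are assumptions:

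- S: share of participants claiming abstinence
- m: share of claims that CO would overturn, taken as equal in both contact modes
- f: share of claimants contacted remotely at visit 2 or 3

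Fully verified percentage = S(1 − m). Pooled percentage = S[1 − (1 − f)m]. Relative excess of pooled over verified = f·m/(1 − m).

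- f = 20%, m = 20%: 0.20 × 0.20/0.80 = 0.05, or 5%
- f = 30%, m = 30%: 0.30 × 0.30/0.70 = 0.129, or 13%
- f = 50%, m = 30%: 0.50 × 0.30/0.70 = 0.214, or 21%

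In absolute terms, with S = 40% and m = 20%, the percentage is 32% if all claimants attend, 36% if half do and 40% if none do. The gap between the extremes is S·m. For S from 30% to 50% and m from 10% to 40% it runs from 0.30 × 0.10 = 3 points to 0.50 × 0.40 = 20 points, with no difference in smoking.

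**Step 4. Setting a verified visit beside an unverified one.** If a fully verified month-3 percentage is compared with an unverified month-6 percentage and smoking has not changed, the apparent rise is m/(1 − m): 11%, 25% and 43% for m = 10%, 20% and 30%.

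**Step 5. Effect of counting absent CO as not verified.** The verified percentage becomes S(1 − f)(1 − m), which is (1 − f) times the fully verified one. It is 20% lower at f = 20%, 30% lower at f = 30% and 50% lower at f = 50%.

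**Step 6. Sample size.** The plan's 264 comes from a 20% incidence of adverse events and reactions and a 95% interval of total width 10 points. An exact Clopper-Pearson interval reproduces it (width 0.0999 at n = 264). It does not depend on the abstinence outcome.

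**The case against.** The strongest reply is that two parallel outcomes are intended. Clinical endpoints describes self-reported and verified abstinence in separate sentences, Table 1 gives them separate rows, the analysis percentage is of those who report abstinence, and the models name a reported and an objective criterion. On that reading a remote self-report and an in-person self-report score alike in the reported series, and nothing is mixed. This is plausible, and no sentence defines a composite. A reader might infer that the plan's percentages do mix verified and unverified successes; the documents permit that but do not establish it. What survives is that the analysis section applies verification to the PPA and never says that two percentages will be reported.

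A reader might also infer that the course from month 3 to month 6 will hide relapse. The plan sets out percentages at each timepoint and models at two timepoints, with no analysis of change over time. The self-reported series has one definition throughout. Step 4 is a caution about an unplanned comparison, not a defect of a planned one.

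The denominator and the handling of absent CO are details that a condensed article may leave to the full protocol or SAP, so their absence is not itself the fault. They appear below only because separating the two series requires them.

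Efficacy is a secondary objective. That is correct and limits the weight of the point.

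**Conclusion.** The point holds in a limited form. Three things rest on the text alone:

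- The face-to-face statement and the Table 1 footnote conflict at visits 2 and 3.
- Verification is tied to contact mode, in wording that does not keep reported and verified abstinence apart.
- An objective relapse criterion is modelled at 12 months without any objective measurement.

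The conflicting CO cut-offs add to the uncertainty about what a verified abstainer is.

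Overstatement of efficacy is conditional. It follows only if claims with and without CO are pooled. Its size cannot be derived from the documents: 5% to 21% relative is an illustration under assumed values of f and m and assumes equal misreporting in both contact modes. The documents do not support an unconditional statement that efficacy and its durability are inflated.

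The change is worth making because it is cheap and the abstinence percentages have no comparator. The primary safety endpoint, the 264 and the 300 are unaffected.

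**What to change.** 1. **Visits and follow-ups.** Reconcile the face-to-face statement with the Table 1 footnote, so that it is clear whether remote contact is allowed at visits 2 and 3.
2. **Self-reported series.** In the analysis section, report 7-day and 15-day PPA at all visits with no CO correction, as the only series to be compared across timepoints. At visit 1 (day 7) a 15-day window reaches back before the quit day, so that entry needs a note.
3. **CO-verified series.** Report it at visits 1 to 3 only, using one stated cut-off after Clinical endpoints and Carbon monoxide measurement have been reconciled. Use all treated participants as denominator and count absent CO as not verified. Beside it, give the rate among those with a CO reading and the number without one at each visit.
4. **Relapse models.** Use the objective criterion at day 25 only, and the reported criterion at 12 months.

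**Cost.** One footnote or sentence and a few lines of analysis wording; all the data are already planned. The downside is not small if remote contact is common. The conservative verified rate falls in proportion to the share of claimants without CO, by 20% to 50% in relative terms if 20% to 50% of them are remote. It still depends on contact mode, now downwards, because truthful remote abstainers count as not verified. It should be labelled a lower bound and read with the rate among those measured. The self-reported series is the one freed from dependence on contact mode in its scoring.
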